#### Primary Outcome Measures—Predictive Capacity

To assess the capacity of DT turning measures to predict performance in a civilian ambulatory task (CAT), participants will navigate through an uncontrolled pedestrian environment while wearing inertial sensors as shown in Figure 1. A walking route of standardized length will be established at each site for participants to walk around the testing location. Common elements at each site's walking route will be written instructions and landmark-based directions to follow (e.g., take the second set of doors on your right). Each site's walking route will require participants to ambulate around public areas and will take ~7 min to complete. Participants will be required to navigate through crowded hallways, ascend and descend stairs, and scan for pedestrian traffic. A trained research assistant will accompany the participant throughout the entire route and provide verbal commands. The research assistant will remain behind the participant to not interfere with the navigation, but close enough to assist the participant in case of a loss of balance. Secondary landmarks will be known by the research assistants. If the participant misses a landmark, the research assistant will notify the participant once he/she reaches the secondary landmark, and the research assistant will instruct the participant that he/she traveled the wrong way and reread the instruction. The route will end in the initial testing area. The primary outcome of the CAT will be the time required to complete the route. Secondary outcome measures will include the peak head and trunk turning velocity, the head–body coordination throughout the course, and the number of landmarks identified and missed.

To assess the capacity of DT turning measures to predict performance in a military-relevant task, participants will complete a simulated urban patrol task (SUP, Figure 2). During the SUP task, participants will navigate an environment containing two small rooms separated by a doorway. The environment will be created using portable partitioning boards to compartmentalize a medium-sized clinical or laboratory space. Each compartmentalized room within the environment will contain five 5-cm diameter targets, surrounded by LED lights. The targets will be placed in areas that are not visible from the adjoining compartment. The LED lights surrounding each target will denote either hostile (illuminated red) or friendly (illuminated blue) targets.

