#### Sample Size

Sample size calculation and power analysis were based on Hedge's *g* effect sizes determined through preliminary data on turning in people with mTBI (21); we observed a range of Hedge's *g* effect sizes of −1.09 to −1.32 between the peak lumbar turn velocity of healthy controls and people with mTBI and residual symptoms when performing 90° turns. With 50 civilian participants per group and the midrange effect size from our preliminary work, we will have 90% power to detect differences in peak lumbar turning velocity between healthy controls and people with mTBI with a two-tailed 0.01 significance level if we observe at least 65% of the effect size we observed previously (*g* = −1.20). For the second goal, the power analysis was based on the correlation between clinic-based peak turning velocity and the duration of walking bouts, a common measure of daily ambulatory function, exhibited during daily, unmonitored activities at home (Pearson ρ = 0.362, data obtained from DoD #W81XWH-15-1-0620). With 140 planned participants (100 civilian participants and 40 active-duty participants), we will have 97% power to detect a correlation between the lumbar turning velocity measured in the clinic and daily function with a two-tailed 0.01 significance level if we observe the same effect size. Power calculations were performed in G^*^Power 3.1.9.2 (68).

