#### Statistical Analysis

To evaluate the capability of objective, DT turning measures to discriminate between healthy controls and people with mTBI, we will construct receiver operating characteristic (ROC) curves using each objective turning outcome and clinical assessment of activity. The area under the ROC curve (AUC) will be calculated, and AUC confidence intervals will be generated through a bootstrapping procedure. We will compare the AUCs and confidence intervals between each objective turning measure and clinical assessment of activity using tests of equality and a 0.05 significance level with Holm-Bonferroni corrections to adjust for multiple comparisons.

To assess the capacity of DT turning measures to predict performance in civilian or military-relevant tasks, we will use Pearson correlation coefficients and linear regression models. Pearson correlation coefficients will compare the linear relationship between objective turning outcomes and the primary outcome of task completion time during the CAT and throughput during the SUP tasks within participants with mTBI, healthy control participants, and all participants together. To determine how changes in objective turning measures correspond to changes in functional performance, linear regression models will be built for each objective turning measure that was significantly associated with functional performance. The primary outcomes for the civilian and military-relevant tasks will be modeled as the dependent variable. To account for potential differences in performance between civilians and active-duty SMs, a group effect will be included as a covariate. Beta coefficients will be interpreted to identify the relative change in objective turning measures that are associated with changes equal in magnitude to 1 standard deviation of the healthy control participants' performance.

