To determine clinically viable measures of turning based on clinometric properties, we will calculate the repeatability and minimum detectable difference using a Bland-Altman framework on the subset of participants who complete two blocks of turning tasks (80, 81). Linear mixed models will be fit for each objective outcome measure and task combination, with site location included as a covariate. Random intercepts will be fit for each participant to control for repeated measurements. Repeatability and minimum detectable change will be assessed using the within-subject error term for each outcome measure. Minimum detectable change will be calculated as $1.96^{*}\sqrt{2}$ times the within-subject error of the civilian control, military control, and civilian mTBI groups separately, as well as all groups combined. Differences across sites will be assessed using the standard error of effect of site location. Intraclass correlation coefficients will assess the absolute agreement and consistency of the outcomes across difference testing blocks. Outcomes with ICCs >0.7 will be identified as having good agreement and consistency for clinical implementation. Bias and learning effects will be considered by directly investigating the mean and median difference between blocks using a Bland-Altman framework (80, 81).

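### The CAT regressions pool times from four site-built routes with no site term and omit mTBI status, so the slope of performance on turning mixes route and case-control differences with the within-group relation

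*Protocol article*

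**What the plan says.** All locations are in the Protocol article.

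- **Primary Outcome Measures—Predictive Capacity.** The CAT primary outcome is time to finish the route. "A walking route of standardized length will be established at each site for participants to walk around the testing location". The setting is an uncontrolled pedestrian one. The sites share written, landmark-based directions, stairs, crowded hallways and a duration of about 7 minutes.
- **Phase 1, Participants.** Three civilian sites test 50 people with mTBI and 50 controls. The 40 service-member controls are all tested at Fort Sam Houston.
- **Statistical Analysis.** Pearson correlations of turning with CAT time and with throughput on the simulated urban patrol (SUP) are run "within participants with mTBI, healthy control participants, and all participants together". Measures with a significant association then get a linear regression, with this adjustment: "To account for potential differences in performance between civilians and active-duty SMs, a group effect will be included as a covariate". No site term and no mTBI term is stated.
- **Secondary Statistical Analyses.** The repeatability models are fitted "with site location included as a covariate".
- **Sample Size.** This goal is powered on the pooled sample: "With 140 planned participants (100 civilian participants and 40 active-duty participants").
- **Refinement of Tasks and Outcomes.** Correlation with the civilian task and correlation with the military task are two of the four ranking criteria. The group in which the correlation is taken is not named.

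**The concern.** Two sources of variation in CAT time have nothing to do with whether turning predicts performance within a group of people, and the stated model removes neither.

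**Route.** Stairs, crowding and landmarks are local. The civilian/service-member term is the same variable as an indicator for Fort Sam Houston, so it absorbs that one route and leaves differences among the three civilian routes in the residual. If turning does not differ by site, the association is diluted. If turning does differ by site, the association is biased.

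**mTBI status.** The regression is meant to show how a change in turning corresponds to a change in performance, and its coefficient is converted into the turning change that matches 1 SD of control performance. Without mTBI status, that coefficient is a blend of the within-group slope and the case-control difference. The blend depends on the recruited mix of 50 cases to 90 controls.

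The same holds for the correlation in all participants. If that correlation is the one ranked, a measure that separates cases from controls well is credited under AUC and again under predictive capacity.

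**Working it through.** **1. The stated power.** Inputs from Sample Size: "Pearson ρ = 0.362", N = 140, two-tailed 0.01. By Fisher's z, power = Φ(atanh(r)·√(N−3) − 2.576) = Φ(0.3792 × 11.705 − 2.576) = Φ(1.862) = 0.969. The stated 97% reproduces, but it treats the 140 as one homogeneous sample.

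The same formula applied to the strata at r = 0.362 gives 51% for the 50 with mTBI and 83% for the 90 controls.

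**2. Route differences unrelated to turning.** Let k be the between-route SD divided by the within-route SD (assumed; the document gives none). Then r falls to 0.362/√(1+k²).

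| k | r | Power at 0.01, N = 140 |
|---|---|---|
| 0 | 0.362 | 97% |
| 0.5 | 0.324 | Φ(3.931 − 2.576) = 91% |
| 0.75 | 0.290 | Φ(3.490 − 2.576) = 82% |
| 1.0 | 0.256 | Φ(3.064 − 2.576) = 69% |

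**3. Route differences when turning also differs by site.** Assume no true association, CAT offsets of −1, 0 and +1 SD across the three civilian sites, and turning offsets a quarter or a half of that. In simulation, the regression with only the civilian/service-member term rejects at 0.05 in about 20% or 60% of studies. With a site term it rejects in about 5%.

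**4. Omitted mTBI status in the planned regression.** Assume no within-group association. Turning is lower by g = 1.20 SD in mTBI (the midrange value in Sample Size) and CAT time is longer by d SD (assumed). After the civilian/service-member term is removed, the mTBI indicator has sum of squares 100 × 0.5 × 0.5 = 25, and 140 − 2 = 138 degrees of freedom remain. The expected partial correlation is about

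−25gd / √[(138 + 25g²)(138 + 25d²)].

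For d = 0.5 this is −15/√(174 × 144.25) = −0.095. For d = 0.3 it is −9/√(174 × 140.25) = −0.058. For d = 1.2 it is −36/174 = −0.207. Simulation of the regression at n = 50/50/40 gives mean values of −0.058, −0.094 and −0.207 for d = 0.3, 0.5 and 1.2, and these rejection rates:

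| CAT shift d | Planned model, 0.05 | Planned model, 0.01 | With mTBI term, 0.05 (0.01) |
|---|---|---|---|
| 0.3 | 10% | 3% | 5% (1%) |
| 0.5 | 20% | 7% | 5% (1%) |
| 1.2 | 69% | 45% | 5% (1%) |

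Both levels are shown because Sample Size uses 0.01 for this goal, while Statistical Analysis states 0.05 only for the AUC comparisons.

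**5. The unadjusted correlation in all participants.** With p = 50/140 and v = p(1−p) = 0.230, the induced correlation has size vgd/√[(1+vg²)(1+vd²)]. For g = 1.20 and d = 0.5 this is 0.116, significant at 0.01 in 11% of studies. For d = 1.0 it is 0.215, significant in 49%.

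**The case against.** Several arguments on the other side are sound and limit the point.

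- **The stratified correlations exist.** A reader might infer that every predictive-capacity analysis is confounded by mTBI status. That is not so: the correlations within mTBI and within controls are free of it. They are not free of route differences, the control stratum still mixes civilians and service members, and the mTBI stratum alone has about 51% power at 0.01.
- **The routes share more than length.** The direction format, stairs, crowded hallways and a duration near 7 minutes are common, and duration is the outcome itself. A between-route SD as large as the within-route SD is therefore the far end of the range.
- **SUP.** One might extend the site argument to SUP because each site sets up its own rooms. The document describes a prescribed layout with portable partitions and a fixed number of targets, and reports no difference by site. The site point is confined to CAT.
- **Ranking.** One might say that route dilution distorts the ranks. Dilution unrelated to turning shrinks every measure's correlation with the same CAT time by the same factor, so the order is unchanged. Only confounding can reorder measures, and the ranking section does not say that the pooled correlation is used.
- **Estimand.** For prediction in a mixed population, a pooled correlation that runs partly through mTBI is not a type I error. This stands as a reason to keep the pooled correlation. It does not rescue the regression, whose stated aim concerns how changes in turning correspond to changes in performance.
- **Condensed article.** A full analysis plan may list more covariates. Yet the article names the covariate and its purpose here, and names site in the repeatability models.

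**Conclusion.** The point holds for CAT in respect of site, and for both tasks in respect of mTBI status in the regressions and in the correlation across all participants. The one stated covariate coincides with a single site and leaves the three civilian routes and the case-control difference unadjusted.

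The size depends on shifts the document does not give. With the planning value of 1.20 for turning, false rejection at 0.05 runs from about 10% to 70% as the assumed CAT shift goes from 0.3 to 1.2 SD. At 0.01 it runs from 3% to 45%. The upper end assumes that mTBI slows CAT as much as it slows turning, which nothing in the document supports. The loss of power from 97% to 91% or 69% likewise rests on an assumed spread between routes.

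Because the effect sizes are assumed and stratified correlations are already planned, this should be fixed but does not invalidate the predictive-capacity goal.

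**What to change.** 1. In the CAT regressions, enter site as a four-level fixed effect in place of the civilian/service-member term, which it contains, and add mTBI status.
2. In the SUP regressions, keep the civilian/service-member term and add mTBI status.
3. Report partial correlations beside the pooled Pearson correlation: adjusted for site and mTBI status for CAT, and for service-member and mTBI status for SUP. Adjust the within-mTBI and within-control CAT correlations for site.
4. State in the ranking procedure that the adjusted correlation is the one ranked.

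For CAT this adds two degrees of freedom for site beyond the existing term and one for mTBI status, three in all at N = 140. Both variables are known for every participant, so the change is to wording and code only.

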### Secondary Statistical Analyses

To evaluate if turning outcomes have added value over standard clinical assessments of physical function, base multivariate logistic regression models will be constructed for each clinical assessment of physical function (e.g., FGA, HiMAT). A “base + 1” logistic regression model will be built by adding the objective turning measure with the highest AUC as described above. ROC curves will be constructed for the base and “base + 1” models, and the AUC calculated and compared using likelihood ratio tests. If the AUC from the “base + 1” model is greater than the AUC of the base model, then the process will be repeated iteratively—the outcome measure with the next largest univariate AUC will be added to the “base + 1” logistic regression model to create a “base + *n*” model until the addition of outcomes does not significantly change the AUC.

To evaluate if objective turning measures will be associated with impairments in ICF model components, including body functions and structures, activities, and participation domains, Pearson and Spearman correlation coefficients will be implemented separately within healthy civilian control participants, healthy active-duty control participants, and civilians with mTBI. Linear regression models with ICF impairments (Table 2) as dependent outcomes and main effects of objective turning outcomes, group, and the group ^*^ turning outcome interaction will assess whether the association between objective turning outcomes and ICF function varies by group through the interaction term. A 0.05 significance level will be used with stepwise Holm-Bonferroni corrections to adjust for multiple comparisons.

To determine clinically viable measures of turning based on clinometric properties, we will calculate the repeatability and minimum detectable difference using a Bland-Altman framework on the subset of participants who complete two blocks of turning tasks (80, 81). Linear mixed models will be fit for each objective outcome measure and task combination, with site location included as a covariate. Random intercepts will be fit for each participant to control for repeated measurements. Repeatability and minimum detectable change will be assessed using the within-subject error term for each outcome measure. Minimum detectable change will be calculated as $1.96^{*}\sqrt{2}$ times the within-subject error of the civilian control, military control, and civilian mTBI groups separately, as well as all groups combined. Differences across sites will be assessed using the standard error of effect of site location. Intraclass correlation coefficients will assess the absolute agreement and consistency of the outcomes across difference testing blocks. Outcomes with ICCs >0.7 will be identified as having good agreement and consistency for clinical implementation. Bias and learning effects will be considered by directly investigating the mean and median difference between blocks using a Bland-Altman framework (80, 81).

To determine whether healthy active-duty SMs perform turning tasks differently than healthy civilians, we will fit linear regression models for each turning outcome with main effects of group (active-duty SMs vs. civilians) and adjusted for age, body mass index, and other potential covariates. Inferences will be made using a significance level of 0.05 and a Holm-Bonferroni adjustment for multiple comparisons. If we find outcomes significantly differ between active-duty populations and control populations, we can conclude that population-specific normative values are needed. Given the large sample size of active-duty SMs and controls, we will then separate active-duty and civilian control groups for future analyses using those outcomes with significant differences between active-duty and civilian control participants. If we fail to find differences between active-duty and civilian control groups, it suggests performance does not vary by service status, and normative means, standard deviations, and minimum detectable changes will be calculated by combining data from all healthy control participants. We will also compare the distributions of performance using interval estimators to determine the extent to which the range of performance overlaps between active-duty SMs and civilians.

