Currently, RTD decisions are based on self-reported symptoms, objective measures that assess a single system, or standardized physical tests that lack ecological validity for warrior tasks or battle drills. Duty-readiness is primarily assessed using patient-reported symptoms (13–16) and through batteries of clinical tests designed to detect single-system impairments in isolated sensory, balance, or cognitive domains. Decisions that hinge on self-reported symptoms do not assess function (12), and it is unclear whether self-reported symptoms are associated with job performance decrements that would constitute a tangible risk to SMs or their units. While persistent symptoms have been associated with lower quality of life and community integration (17–19), the impact of symptoms on comprehensive, functional performance is poorly understood (20, 21). Recently, the rehabilitation community has recognized the need to measure a multifaceted battery of assessments to characterize mTBI recovery (22–24), but these batteries remain a compilation of single-domain clinical assessments and may not be representative of the demands imposed by daily life and military activities (12, 25–29). The majority of warrior tasks (urban assault, building breaching, movement to contact, etc.) require the constant integration of complex sensory stimuli (visual, vestibular, and proprioceptive) while under cognitive load during movement in extreme and varying physical conditions (30, 31).

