Quantifying turning performance has traditionally been difficult in clinical settings, but recent advances in wearable sensors have enabled objective, robust, reliable, and sensitive assessments of turning performance in other clinical populations (45, 55–59). This project is designed to transition our previous research findings (8, 9, 21, 45, 55–59) into clinical settings for improved assessments after mTBI by evaluating objective dual-task (DT) turning measures for use as rehabilitative outcomes and as tools for RTD assessments. Therefore, the first goal of this study is to assess diagnostic accuracy—the added value of objective DT turning measures over standard clinical assessments. We hypothesize (a) that objective turning measures, performed in DT contexts, will improve the diagnostic accuracy relative to standard clinical assessments of physical function among people with mTBI and (b) that objective turning measures, performed in DT contexts, will be associated with impairments in International Classification of Functioning, Disability, and Health (ICF) model components, including body functions and structures, activities, and participation domains (60). The second goal of this study is to determine predictive capacity—if objective DT turning measures predict functional performance in civilian and military relevant tasks. We hypothesize that objective turning measures, performed in DT contexts and obtained in the clinic, will predict functional performance in (a) ecologically relevant civilian environments and in (b) ecologically relevant simulated high-demand battle drills. Our third goal in this study is to assess responsiveness to rehabilitation—the responsiveness of objective DT turning measures to standard vestibular rehabilitation in active-duty SMs with residual mTBI-related symptoms. We hypothesize that objective turning measures, performed in DT contexts, will measurably improve over the course of customary rehabilitation for SMs with mTBI-related residual symptoms.

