**Activities level, ICF**		
*Clinical assessments of activities*		To assess the value of objective measures of DT turning over current clinical assessments of activities
Static sway (ML-RMS of sway)	Assesses static postural stability	
Functional gait assessment (total score)	Assesses dynamic balance by measuring performance on simple and complex gait tasks	
High level mobility assessment tool (total score)	Assesses dynamic balance by measuring performance on rapid and challenging mobility tasks	

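### Added value of turning is tested only against one clinical assessment at a time, which cannot support a claim of added value over the activity-level assessments taken together

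*Protocol article*

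**What the plan says.** The Introduction frames the first goal, diagnostic accuracy, as "the added value of objective DT turning measures over standard clinical assessments". Hypothesis (a) narrows the comparator to assessments of physical function. Table 2 gives static sway, FGA and HiMAT one shared purpose: "To assess the value of objective measures of DT turning over current clinical assessments of activities".

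Secondary Statistical Analyses takes up the question: "To evaluate if turning outcomes have added value over standard clinical assessments of physical function". The method there is that "base multivariate logistic regression models will be constructed for each clinical assessment of physical function (e.g., FGA, HiMAT"). To each base, a "logistic regression model will be built by adding the objective turning measure with the highest AUC as described above". Base and extended models have "the AUC calculated and compared using likelihood ratio tests", and further turning outcomes may be added in turn up to base + n.

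The main Statistical Analysis section is also pairwise. It compares the AUC of each turning measure with that of each activity-level clinical assessment, "using tests of equality and a 0.05 significance level with Holm-Bonferroni corrections". For the added-value models the article gives no rule for combining results across the different bases.

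**The concern.** The turning side of the comparison may accumulate several measures, while the clinical side stays at one test. Suppose turning shares information with a second clinical test that is left out of the base. Turning then gets credit for that shared information, even if it tells the clinician nothing that the other routine tests would not.

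The Introduction describes current duty-readiness assessment as working partly "through batteries of clinical tests designed to detect single-system impairments in isolated sensory, balance, or cognitive domains", and the Discussion makes improvement on standard clinical assessments one of three conditions for quick uptake of the turning tests. A significant single-base result could therefore be reported as added value over standard assessment generally, when it was shown only over one named test.

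**Working it through.** **The plan's own figure.** The article gives no figure for the added-value analysis. Its nearest figure is 90% power for the group difference in peak lumbar turning velocity (Sample Size). With g = 0.65 × 1.20 = 0.78, 50 per group and two-sided 0.01, the noncentrality is 0.78 × √(50/2) = 3.9 on 98 df. The noncentral t gives 89.6%, so the figure reproduces. It concerns a mean difference and says nothing about added value.

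**Inputs from the article.** 50 mTBI and 50 civilian controls (Sample Size); three activity-level tests (Table 2), within a battery given to all participants (Assessment Procedures); likelihood ratio test of base against base + 1.

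**Assumed inputs.** Level 0.05, unadjusted, borrowed from the main analysis. Each clinical test separates the groups by d SD. Tests correlate at r with one another and at q with turning. One turning measure is fixed in advance. Variables are normal with equal covariance in both groups.

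**Construction.** The turning shift is set so that turning adds exactly nothing once all three tests are in the model: d_T = 3qd/(1 + 2r).

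**Closed form.** AUC = Φ(√(D²/2)), where:
- one test: D² = d²
- one test plus turning: D² = (d² − 2q·d·d_T + d_T²)/(1 − q²)
- three tests, with or without turning: D² = 3d²/(1 + 2r)

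Case A, d = 0.6, r = 0.4, q = 0.6: d_T = 1.08/1.8 = 0.60.
- one test: D² = 0.36, AUC 0.664
- one test plus turning: D² = (0.36 − 0.432 + 0.36)/0.64 = 0.45, AUC 0.682
- three tests: D² = 1.08/1.8 = 0.60, AUC 0.708

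Turning appears to improve each single test, yet the three tests alone already do better and turning adds nothing to them.

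Case B, d = 0.5, r = 0.8, q = 0.65: d_T = 0.975/2.6 = 0.375.
- one test: D² = 0.25, AUC 0.638
- one test plus turning: D² = (0.25 − 0.24375 + 0.140625)/0.5775 = 0.254, AUC 0.639
- three tests: D² = 0.75/2.6 = 0.288, AUC 0.648

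When the clinical tests largely repeat one another, the gap almost closes.

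**Simulated rate of declaring added value (approximate %, 1-df likelihood ratio test at 3.841):**

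| d | r | q | given single base | at least one of three | all three | joint base |
|---|---|---|---|---|---|---|
| 0.5 | 0.5 | 0.5 | 11 | 18 | 4 | 5–6 |
| 0.5 | 0.5 | 0.65 | 18 | 35 | 6 | 5–6 |
| 0.6 | 0.4 | 0.6 | 31 | 49 | 14 | 5–6 |
| 0.6 | 0.5 | 0.7 | 31 | 55 | 10 | 5–6 |
| 0.5 | 0.8 | 0.5–0.65 | 5–7 | 9–12 | 2–3 | 5–6 |

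**Two tests only.** If the clinical set is just FGA and HiMAT, the first three rows become 8%, 12% and 15% per base, and 4%, 5% and 8% for both.

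**Wider assumptions.** A second three-test grid used d of 0.5 or 0.8, r from 0.2 to 0.6, and turning built as the sum of the tests plus noise, with 50% or 80% of its within-group variance explained by them. Rates ran from 9% to 91% per base and from 3% to 79% for all three, against 5–7% with the joint base. The top end needs weakly correlated tests, each with a large effect. The table is therefore neither a bound nor a forecast.

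**The case against.** The strongest reply is that the analysis is not wrong for the question it asks. In every scenario above, turning truly does add to the single test in the base, so rejecting that null is correct. A reader might infer from the 31% or 55% that the planned test has an inflated false-positive rate. It does not. The excess arises only when a single-test result is relabelled as added value beyond the whole set. The "at least one" column also rests on a decision rule that appears nowhere in the article. Under an all-three rule the excess is small or absent in most rows.

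Second, the comparator wording can be read as each assessment in turn, and the plan is consistent in treating it so. The Introduction's remark on batteries covers sensory, balance and cognitive domains, which is not the same set as sway, FGA and HiMAT. The article nowhere says that clinicians use those three together. Including sway rests on Table 2, since Secondary Statistical Analyses names only FGA and HiMAT as examples.

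Third, "multivariate" is not explained. It may refer to covariates that the full protocol or SAP lists.

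Fourth, this is a secondary analysis, and the ranking under Refinement of Tasks and Outcomes for Future Clinical Use does not draw on it.

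All of this stands, and it limits the point to a matter of scope. What remains is that no described analysis sets turning against the activity-level assessments jointly, while the goal, the Table 2 purpose and the Discussion are all worded in the plural.

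**Conclusion.** The point holds as a gap between the claim and the model, and it is cheap to close. The single-test models answer a valid but narrower question. They cannot by themselves support a statement that turning adds to the clinical assessments of activity taken together.

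Under the table's assumptions, a measure with nothing to add beyond three tests is credited over a given single test in about 5–7% (r = 0.8) to about 31% of trials (d = 0.6, r = 0.4–0.5). The range is about 9% to 55% for at least one test and about 2% to 14% for all three, against 5–6% with a joint base. Effect sizes and correlations are all assumed. The simulation also ignores that the turning measure is chosen for its AUC in the same data, which would tend to raise the rates, and any multiplicity adjustment, which would lower them.

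A reader might go further and conclude that the trial's first goal is tested with the wrong comparator. The documents do not support that: the wording allows an each-in-turn reading, and the measure finally put forward is chosen by other criteria.

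**What to change.** In Secondary Statistical Analyses, add one base logistic model holding static sway, FGA and HiMAT together, add turning to it, and rest any statement of added value over the standard clinical assessments as a set on that comparison. Keep the single-test base models as planned, and word each conclusion as added value over that named test only. If a joint base is what "multivariate" was meant to convey, the sentence only needs to say so.

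No new data are needed. The cost is one more model with two more base parameters on 50 cases and 50 controls, and probably a smaller apparent gain for turning.
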